## Abstract

**Background:**

Resistant hypertension is a specific condition that affects approximately 10% of subjects with hypertension, and is characterized by persistently high blood pressure levels even using therapy of three or more antihypertensive agents or with blood pressure control using therapy with four or more antihypertensive agents. Changes in lifestyle, such as physical exercise, are indicated for controlling blood pressure. However, investigating studies about this therapy in individuals with resistant hypertension are few.

**Methods/design:**

This is a randomized controlled clinical trial. Forty-eight patients with resistant hypertension will be submitted to perform four short-term interventions: aerobic exercise sessions (mild-, moderate- and high-intensity) and control session, in random order and on separate days. After the short-term sessions, the patients will be randomly allocated into four groups for 8 weeks of follow-up: mild-, moderate- and high-intensity aerobic exercise, and a control group. The primary outcome is the occurrence of blood pressure reduction (office and ambulatory analysis, and acute and chronic effects). Secondary outcomes are autonomic and hemodynamic mechanisms: cardiac and vasomotor autonomic modulation, spontaneous baroreflex sensitivity, forearm blood flow and vascular resistance.

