For subjects with resistant hypertension, there are few studies involving physical exercise. Clinical trials [29–32] have identified significant reductions in SBP and DBP levels after 12 weeks of continuous moderate aerobic exercise training (based on lactate concentration) and strength training (resistance exercise in a pool). Recently, a crossover trial investigated short-term exercise (mild and moderate intensity) effects in resistant hypertension and found significant reductions in both SBP and DBP levels at both intensities [33]. These studies show the importance of physical exercise as a therapeutic strategy for this population. However, it is still unclear which physical exercise characteristics can result in better outcomes in follow-up studies for patients with resistant hypertension, as well as the possible mechanisms linked to adjustments in BP levels. Exercise characteristics, such as intensity, duration, frequency and type, are associated with different BP responses. Aerobic exercise intensity is a characteristic that seems to influence the magnitude and duration of PEH, but there is no consensus about the magnitude of hypotension and/or the intensity which is more effective in reducing BP levels. Eicher et al. [34] reported that high-intensity interval-training exercise promotes PEH; however, other authors found that lower intensities have been more effective in reducing BP levels [35]. Therefore, studies are inconclusive in presenting the most effective intensity or identifying differences in hypotensive responses to varying intensities used in clinical trials [17, 25, 36–39].

Thus, a trial testing the efficacy of different intensities of aerobic exercise to control BP is necessary and important. Considering the recent findings on physical exercise in resistant hypertension and different responses to exercise intensities, it is hypothesized that short-term sessions of aerobic exercise of mild, moderate and high intensities can promote PEH as a primary outcome; furthermore, follow-up aerobic exercise training for 8 weeks can reduce the BP levels. Additionally, adjustments are expected in the autonomic and hemodynamic variables, such as reduced sympathetic modulation, increased parasympathetic modulation, improved baroreflex sensitivity, decreased forearm vascular resistance, and a consequent increase in blood flow.

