## Outcomes

### Primary outcome

#### Blood pressure

For the BP measurement in the office, analysis will consider the difference between post-intervention and pre-intervention values. For ambulatory analysis, BP will be considered as sleep and awake periods, and the difference between 24-h post-intervention and pre-intervention values. In the follow-up analysis, baseline BP values (considering control session values without intervention) and post-training BP values will be evaluated.

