## Statistical analysis

### Power and sample size

Sample size was calculated using ABPM as the main outcome. Considering the high variance in the results with resistant hypertensive patients [29, 30] and the meta-analysis results of Fagard [28] with hypertensive patients, BP reduction after endurance training of 7 mmHg from SBP and 5 mmHg from DBP was used in the calculation. In order, to provide 80% power to detect a difference of 3 mmHg between the four distinct conditions (exercise intensity and control), a total of 32 patients are indicated to give sufficient power for the study (*n* = 8 for each group). Considering the possible sample loss, 12 patients will be included in each group.

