### Analysis plan

Intragroup and intergroup differences between dependent variables (BP, autonomic modulation, baroreflex sensitivity, blood flow and vascular resistance) considering pre and post interventions (short-term), baseline and post intervention (dependent factor), and exercise intensities or control (independent factor) will be analyzed by two-way analysis of variance (ANOVA) for repeated measures with the Bonferroni post hoc test. Multiple linear regression will be used for analyzing confounding factors (dietary habits and unsupervised physical exercise practice in the follow-up period). Pearson’s correlation test will be used for analyzing the relation between short-term and long-term results. Intention-to-treat will be considered for the patients with an incomplete follow-up period. A *p* value < 0.05 will be considered significant for all evaluations.

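### The primary outcome is an unranked set of blood pressure endpoints (about 4 to 8 per phase), with 0.05 applied to every evaluation and no error control stated across them

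*Protocol article*

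**What the plan says.** Four parts of the protocol article bear on which blood pressure (BP) result is primary.

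- **Abstract, Methods/design:** "The primary outcome is the occurrence of blood pressure reduction (office and ambulatory analysis, and acute and chronic effects"). This covers two settings and two phases.
- **Outcomes, Primary outcome, Blood pressure:** "For the BP measurement in the office, analysis will consider the difference between post-intervention and pre-intervention values". Then: "For ambulatory analysis, BP will be considered as sleep and awake periods, and the difference between 24-h post-intervention and pre-intervention values". For training: "In the follow-up analysis, baseline BP values (considering control session values without intervention) and post-training BP values will be evaluated". The section names no BP component (systolic or diastolic) and gives no order of importance.
- **Background, last paragraph:** the hypothesis is that "short-term sessions of aerobic exercise of mild, moderate and high intensities can promote PEH as a primary outcome", with the effect of 8 weeks of training added afterwards.
- **Statistical analysis, Power and sample size:** "Sample size was calculated using ABPM as the main outcome". The inputs are reductions after endurance training of 7 mmHg systolic and 5 mmHg diastolic. No ambulatory period is named, and neither component is given priority.

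On error control, the Analysis plan specifies a two-way repeated-measures ANOVA with the Bonferroni post hoc test, and then a single rule: a p "value < 0.05 will be considered significant for all evaluations".

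**The concern.** A trial with several primary endpoints needs either a rule for combining them or an adjustment across them. Here the primary outcome spans office and ambulatory pressure, acute and chronic effects, several ambulatory summaries and two BP components. The only stated threshold is 0.05 for each evaluation. The Bonferroni step adjusts contrasts among conditions and time points inside one ANOVA. It does nothing across systolic and diastolic, office and ambulatory, or sleep, awake and 24-h values, because each of these is a separate dependent variable with its own ANOVA.

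At stake is the claim that exercise lowers BP in resistant hypertension. With 12 patients planned per group, and a Discussion that looks ahead to use in clinical practice, one isolated positive among several BP results could be presented as the primary finding.

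**Working it through.** **Figures in the plan.** The article gives no error rate across endpoints, so there is none to reproduce. Its only related figure is the sample size: 8 per group for 80% power to detect 3 mmHg, raised to 12 for losses. No standard deviation (SD) is given, so this cannot be rebuilt. Solving backwards (two groups, two-sided 0.05, normal approximation), SD = 3 / [(1.960 + 0.842) × √(2/8)] = 2.14 mmHg. I use this value only to cost one option under the fix.

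**Counting endpoints.** Components: 2 (systolic and diastolic, both used in the sizing). Phases: 2 (acute and chronic). The number of BP summaries depends on how the ambulatory sentence is read:

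| Reading | Summaries | Per phase (× 2 components) | Both phases (× 2) |
|---|---|---|---|
| Office, ambulatory as one | 2 | 4 | 8 |
| Office, awake, sleep | 3 | 6 | 12 |
| Office, awake, sleep, 24-h mean | 4 | 8 | 16 |

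I do not multiply by intensity, which is the ANOVA factor covered by the Bonferroni post hoc test. Nor do I multiply by the 30- and 60-minute readings, which may be levels of the repeated factor, or by device, since the outcomes section does not say that each device is tested separately.

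**Chance of at least one false positive.** For k independent tests at 0.05 it is 1 − 0.95^k:

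- k = 4: 1 − 0.8145 = 0.186
- k = 6: 1 − 0.7351 = 0.265
- k = 8: 1 − 0.6634 = 0.337

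BP measures on the same patients are positively correlated. For two-sided normal tests with a common pairwise correlation (an assumption; the article gives none):

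| k (one phase) | Independent | Correlation 0.5 | Correlation 0.8 |
|---|---|---|---|
| 4 | 19% | 16% | 11% |
| 6 | 26% | 21% | 14% |
| 8 | 34% | 25% | 16% |

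The smallest entry is about twice the nominal 5%.

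**Which endpoint is main.** The abstract gives equal place to office and ambulatory pressure and to acute and chronic effects. The Background attaches the primary outcome to the acute effect. The sizing attaches it to ambulatory pressure, with reductions seen after training. These three emphases are compatible only if all the endpoints are primary, and that is the situation without error control.

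**The case against.** Several points on the other side have force.

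- **Separate questions.** The Research question section asks about acute and chronic effects separately, and each phase has its own randomisation: order of sessions within patients, then allocation to groups. Pooling both phases into one family of up to 16 tests, with 56% under independence (1 − 0.95^16), exaggerates the problem. This stands, and so the figures here are per phase.
- **Not a minimum of 16.** A reader might infer that at least 16 tests are planned. That requires the 24-h value to be a third ambulatory endpoint beside awake and sleep. The sentence "BP will be considered as sleep and awake periods, and the difference between 24-h post-intervention and pre-intervention values" can also be read with 24 h as the recording window.
- **The sizing variable is not foreign to the primary outcome.** A reader might infer that the trial is sized on something other than what decides success. The article does not support this: ambulatory pressure is part of the primary outcome, and nowhere does the text say which measure decides success.
- **No stated rule that any one result suffices.** That is so. The article is silent on how the endpoints combine, and an analysis plan that is not shown may supply a hierarchy. What remains is what the article does fix: an unranked primary set, 0.05 for every evaluation, and different main endpoints in different sections.

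**Conclusion.** The concern holds in a moderate form. The primary outcome is an unranked set of 4 to 8 BP endpoints per phase (8 to 16 overall), and nothing stated controls error across them. If every BP null hypothesis in a phase is true and each is tested at two-sided 0.05, the chance of at least one false positive is 19% to 34% under independence and about 11% to 25% at correlations of 0.5 to 0.8. The article does not state sidedness or the correlations; both are assumed. The size of the inflation depends on the reading, but its presence does not. The sections also need to be reconciled on which endpoint is primary, a choice that belongs in the protocol itself.

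**What to change.** 1. In the abstract, the primary outcome section and the analysis plan, name one ambulatory BP variable as primary, stating both period and component. This follows the sizing section, which makes ambulatory pressure the main outcome. 24-h systolic pressure is a reasonable candidate, but the sizing does not dictate it, because it uses both components and names no period. The sponsor should choose and justify.
2. State one primary comparison with control for each phase: exercise versus control session for the acute phase, and exercise versus control group for the 8-week phase. Say whether the exercise conditions are combined or one is named in advance.
3. Test the two phases in a fixed, prespecified order, each at 0.05.
4. Make the other component, the other ambulatory periods, office BP and the 30- and 60-minute values secondary.
5. Reconcile the abstract, Background, outcomes and sizing sections on which endpoint is primary.

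**Cost.** The change is mainly wording, and some results now called primary become secondary. The fixed order keeps full alpha for the first test, but the second phase can be claimed only if the first succeeds. Splitting alpha at 0.025 per phase avoids that dependence but is not free. At the implied SD of 2.14 mmHg, n = 2 × [2.14 × (2.241 + 0.842) / 3]² ≈ 9.7, so 10 per group rather than 8 before losses. The Trial status section reports that recruitment was still under way, so the change could be made before analysis.

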**Discussion:**

The importance of exercise for hypertension has been known for decades, but little is known about the effects on patients with resistant hypertension. This study will help to understand whether different aerobic exercise intensities can induce different responses, as well as by what mechanisms adjustments in blood pressure levels may occur.

**Trial registration:**

ClinicalTrials.gov, ID: NCT02670681. Registered on 28 January 2016 (first version); Brazilian Registry Platform Clinical Trials: protocol RBR-5q24zh. Registered on 24 June 2015.

**Electronic supplementary material:**

The online version of this article (doi:10.1186/s13063-017-1985-5) contains supplementary material, which is available to authorized users.

## Background

Systemic hypertension is a multifactorial clinical condition characterized by persistently high blood pressure (BP) levels with systolic BP (SBP) ≥140 mmHg and/or diastolic BP (DBP) ≥90 mmHg [1]. In a particular condition, hypertension can be classified as resistant hypertension, which is characterized by persistently high BP levels even with therapy involving three or more antihypertensive agents in appropriate doses and combinations, or controlled BP in therapy with four or more antihypertensive agents [2], as well as failure to maintain BP levels below 140/90 mmHg, even with the appropriate use of three or more antihypertensive agents and at least one diuretic being necessary [3]. The prevalence of resistant hypertension is highly variable depending on the evaluated population, but approximately 10% of the hypertensive population has this resistance [1].

Given the lack of pharmacological responsiveness of this population, nonpharmacological strategies are encouraged. These include restricting salt intake, reducing alcohol consumption, stopping smoking, losing weight, changing diet and doing regular physical activity [1]. The importance of physical exercise in promoting a reduction in resting BP levels is well established in the academic literature, and is a phenomenon known as post-exercise hypotension (PEH) [4]. PEH could occur due to alterations in diverse mechanisms such as reduced peripheral vascular resistance and/or cardiac output [5–7], increased vasodilator bioavailability [6, 8, 9], reduced sympathetic nerve activity, increased parasympathetic modulation and improved baroreflex sensitivity [10, 11].

Previous studies have found decreased BP levels after a single aerobic exercise session for hypertensive patients [12–21]. There is a wide range of magnitude (between −2 mmHg and −12 mmHg) and duration (between 4 and 16 h) of PEH, which is probably due to individual characteristics and different aerobic exercise protocols (e.g., intensity and duration) [22]. BP reduction is also found in follow-up studies [23–27]. In a meta-analysis of normotensive and hypertensive patients, Fagard [28] showed a 3.3-mmHg decrease in SBP, and 3.5 mmHg for DBP. Such reductions in chronic levels are often more discreet, but very important clinically, where a 2-mmHg reduction may decrease the risk of myocardial infarction by about 6%, and the risk of developing coronary artery disease by 4% [3].

For subjects with resistant hypertension, there are few studies involving physical exercise. Clinical trials [29–32] have identified significant reductions in SBP and DBP levels after 12 weeks of continuous moderate aerobic exercise training (based on lactate concentration) and strength training (resistance exercise in a pool). Recently, a crossover trial investigated short-term exercise (mild and moderate intensity) effects in resistant hypertension and found significant reductions in both SBP and DBP levels at both intensities [33]. These studies show the importance of physical exercise as a therapeutic strategy for this population. However, it is still unclear which physical exercise characteristics can result in better outcomes in follow-up studies for patients with resistant hypertension, as well as the possible mechanisms linked to adjustments in BP levels. Exercise characteristics, such as intensity, duration, frequency and type, are associated with different BP responses. Aerobic exercise intensity is a characteristic that seems to influence the magnitude and duration of PEH, but there is no consensus about the magnitude of hypotension and/or the intensity which is more effective in reducing BP levels. Eicher et al. [34] reported that high-intensity interval-training exercise promotes PEH; however, other authors found that lower intensities have been more effective in reducing BP levels [35]. Therefore, studies are inconclusive in presenting the most effective intensity or identifying differences in hypotensive responses to varying intensities used in clinical trials [17, 25, 36–39].

Thus, a trial testing the efficacy of different intensities of aerobic exercise to control BP is necessary and important. Considering the recent findings on physical exercise in resistant hypertension and different responses to exercise intensities, it is hypothesized that short-term sessions of aerobic exercise of mild, moderate and high intensities can promote PEH as a primary outcome; furthermore, follow-up aerobic exercise training for 8 weeks can reduce the BP levels. Additionally, adjustments are expected in the autonomic and hemodynamic variables, such as reduced sympathetic modulation, increased parasympathetic modulation, improved baroreflex sensitivity, decreased forearm vascular resistance, and a consequent increase in blood flow.

## Rationale

It is known that hemodynamic, humoral and neural changes are associated with hypertension. Pharmacological therapy affects these variables and helps to control BP. However, some subjects with hypertension are nonrespondent to this therapy, and are classified as resistant hypertensive patients. Acute and chronic aerobic exercise reduces BP, thereby adjusting autonomic and hemodynamics, improving parasympathetic modulation, baroreflex sensitivity, vasodilator response and attenuates sympathetic modulation and vascular resistance. Different aerobic exercise intensities could stimulate diverse physiological mechanism responses, and, therefore should produce different adjustments in BP. Even when not responding properly to drug strategies that act on different variables depending on antihypertensive class, it is possible that simultaneous autonomic and hemodynamic adjustments caused by physical exercise promote reduced BP.

## Research question

Is there reduced BP after different short-term aerobic exercise intensities in resistant hypertensive patients? Could reduced BP persist after aerobic training?

What mechanisms (autonomic and hemodynamic) could be responsible for PEH in these resistant hypertensive patients after short-term and long-term aerobic exercise at different intensities?

## Methods/design

This is a randomized controlled clinical trial with single-blind data analysis. The Standard Protocol Items: Recommendations for Interventional Trials (SPIRIT) flow chart and enrollment schedule, interventions and assessments for the trial are given in Fig. 1 and the SPIRIT Checklist in Additional file 1. Figure 2 presents the experimental research design stages. In addition to ongoing medical monitoring, all individuals will be assessed by anamnesis, anthropometric measurements, biochemical tests, echocardiogram, cardiopulmonary exercise test, information about lifestyle (including dietary habits), and habits/history of physical activity before each short-term intervention and after the follow-up period.

**Fig. 1 Fig1:**
[figure not shown]
Standard Protocol Items: Recommendations for Interventional Trials (SPIRIT) schedule of enrollment, interventions and assessments

**Fig. 2 Fig2:**
[figure not shown]
Flow chart of selection and interventions. BMI: Body Mass Index. kg: kilogram. m: meter

### Eligible participant and exclusion criteria

Patients with resistant hypertension, who are aged between 40 and 70 years, will be recruited from the Lauro Wanderley University Hospital at the Federal University of Paraiba, Brazil, being men or women (women must be postmenopausal, nonmenstruating for at least 1 year and not using hormone replacement therapy), with Body Mass Index ˂40 kg/m^2^ and able to do physical exercise. Patients with resistant hypertension when BP levels are ≥140/90 mmHg for SBP/DBP, respectively, using three or more antihypertensive agents in appropriate doses and combinations, or with controlled BP using four or more antihypertensive agents, will be considered [3] in addition to considering ambulatory BP monitoring (ABPM) records. Controlled BP will be considered for SBP and DBP: at 24 h <130 mmHg and <80 mmHg; awake <135 mmHg and <85 mmHg; and sleeping <120 mmHg and <70 mmHg [40].

After clinical assessment and verifying medical records and biochemical data, patients can be excluded for having a history of ischemic stroke, coronary heart disease, chronic obstructive or restrictive pulmonary disease, peripheral arterial disease, hypo/hypernatremia, hyper/hypothyroidism, chronic atrial fibrillation or a change in drug therapy for an experimental protocol. In the follow-up phase, patients who do not participate in 90% of the exercise training sessions, miss three consecutive training sessions or present any osteoarticular disease that prevents them from continuing the physical training program will be considered as sample loss.

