### Random allocation sequence

Randomization will be done using a sealed opaque envelope. All the patients will be submitted to perform four short-term interventions (within design): mild aerobic exercise, moderate aerobic exercise and high-intensity aerobic exercise and a control session, in random order and on separate days. After the short-term sessions, all the patients will be randomly allocated into four groups and followed up for 8 weeks (between design): mild aerobic exercise group, moderate aerobic exercise group, high-intensity aerobic exercise group and the control group.

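### The 8-week comparison mixes patients with controlled and uncontrolled BP, and the article describes neither balancing nor adjustment for this, so it carries avoidable variance

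*Protocol article*

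**What the plan says.** The eligibility section of the protocol article defines two routes into the trial. The first is "Patients with resistant hypertension when BP levels are ≥140/90 mmHg for SBP/DBP, respectively, using three or more antihypertensive agents". The second is "or with controlled BP using four or more antihypertensive agents, will be considered". Control is defined by ambulatory monitoring (ABPM): "Controlled BP will be considered for SBP and DBP: at 24 h <130 mmHg and <80 mmHg", with further limits for the awake and sleeping periods.

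On allocation, the section on the random sequence states "Randomization will be done using a sealed opaque envelope" and "After the short-term sessions, all the patients will be randomly allocated into four groups and followed up for 8 weeks". It names no balancing factor.

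The sample size section takes ABPM as the main outcome and aims "to provide 80% power to detect a difference of 3 mmHg between the four distinct conditions", with 8 patients per group raised to 12 to allow for losses. It gives no standard deviation, only the remark "Considering the high variance in the results with resistant hypertensive patients".

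The analysis plan specifies a two-way repeated-measures ANOVA with Bonferroni post hoc tests. A regression for confounders lists dietary habits and unsupervised exercise. Baseline BP and control status appear in neither.

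**The concern.** The entry rule splits patients on the level of the very variable that the trial tries to lower. Someone already below the ABPM limits may fall less after training than someone well above them. With only 12 patients per arm, chance alone can give one arm noticeably more controlled patients than another, and a difference in response would then carry into the comparison of intensities.

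The information needed to deal with this exists in time. The 8-week allocation follows the short-term sessions, and the control session, which supplies the follow-up baseline, includes ABPM. The article goes as far as naming its adjustment factors but leaves out the one that its own eligibility rule creates. At stake is the precision of the 8-week between-group comparison.

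**Working it through.** **The plan's own figure.** The calculation for 8 per group cannot be reproduced, because no SD is given. Solving back for two groups, two-sided 5% and 80% power: SD = 3 × √(8/2) / (1.96 + 0.84) = 6 / 2.80 = 2.14 mmHg (1.99 with the t distribution).

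**Inputs.** From the article: 48 patients, four arms of 12, target 3 mmHg. Assumed, because the article gives neither:
- share controlled, p: 30-50%, taken as 14, 19 or 24 of 48 patients;
- response gap, D (how much less controlled patients respond): 3-6 mmHg. For scale, the sample size section uses a training effect of 7 mmHg for systolic BP.

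**Step 1: imbalance between two given arms.** With 48 patients split at random into four arms of 12, the number of controlled patients per arm is hypergeometric. The SD of the difference in share between two arms is √[2p(1−p)/12 × 48/47], which is 0.189 at p = 0.3 and 0.206 at p = 0.5, or about 2.3 to 2.5 patients.

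| Controlled of 48 | Median difference, given pair | Given pair differs by ≥4 | Given pair differs by ≥6 | Most vs least loaded arm differ by ≥4 | Most vs least loaded arm differ by ≥6 |
|---|---|---|---|---|---|
| 14 | 2 | 12% | 1.2% | 40% | 6% |
| 19 | 2 | 15% | 2.1% | 47% | 10% |
| 24 | 2 | 16% | 2.4% | 49% | 11% |

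**Step 2: shift in the contrast** = (difference in controlled patients / 12) × D.
- Typical pair: 2/12 × 3 = 0.5 mmHg to 2/12 × 6 = 1 mmHg.
- Difference of 4: 4/12 × 3 = 1 mmHg to 4/12 × 6 = 2 mmHg, one to two thirds of the target.
- To reach 3 mmHg: 6 of 12 at D = 6, or 12 of 12 at D = 3.

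**Step 3: effect on precision.** Mixing the two kinds of patient adds a patient-level SD of D√[p(1−p)] to the change in BP: 3 × √0.21 = 1.4 mmHg at the low end, 6 × √0.25 = 3.0 mmHg at the high end. The upper part of this range exceeds the whole SD of about 2.0-2.1 mmHg that 8 per group implies.

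What adjustment recovers depends on the unstated SD within strata. Take p = 0.5, D = 5, 12 per arm and an unadjusted two-sided t-test for 3 mmHg. If the within-stratum SD is 2.0 mmHg, mixing raises the standard error of an arm difference from 0.82 to 1.31 and lowers power from 94% to 59%. If it is 5 mmHg, the standard error goes from 2.04 to 2.28 and power from 29% to 24%.

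**The case against.** Several objections have force.

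- **The driving inputs are assumed.** This stands. If controlled patients respond as much as the others, nothing is lost beyond what any unmodelled factor costs.
- **Randomisation makes chance imbalance sampling error.** This stands. A reader might infer that the comparison would be biased, reflecting who was allocated and not the exercise. It would not: the imbalance is variance, and the ANOVA error term already includes it. A gap in baseline level also largely cancels in the pre-post contrast; only differential response and regression to the mean remain.
- **The effect does not rival 3 mmHg.** This stands. A reader might infer that it does from the 40-49% chance that some arms differ by 4 or more, but that figure is for the most and least loaded of four arms. For a given pair it is 12-16%. At D = 6, a shift of 3 mmHg or more occurs in 1.2-2.4% of trials for a given pair and 6-11% for any pair. It becomes likelier only with a larger gap or with arms reduced to 8.
- **Silence is not a decision.** A condensed article may leave stratification to the full protocol. The article does not say that allocation is simple, so one can say only that no balancing is described. The analysis plan is less open to this defence, since it states a model and lists its adjustment factors.
- **Mixed eligibility is deliberate.** It follows the definition of resistant hypertension that the article cites, and the point does not challenge it.

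**Conclusion.** The point holds as one of precision in the 8-week between-group comparison. With 30-50% of patients controlled and a response gap of 3-6 mmHg, both assumed, the typical shift between two given arms is 0.5-1 mmHg. In 12-16% of trials it is at least 1-2 mmHg, or one to two thirds of the target difference. Between two exercise arms the gap acts in full. Against the control arm the shift is smaller if only training produces it.

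The acute phase is unaffected, because each patient undergoes all four sessions. The documents do not support a claim of bias, of a shift that generally matches 3 mmHg, or of a decision against stratification. This is a low-cost improvement, not a flaw that invalidates the design.

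**What to change.** Analyse the 8-week BP outcome by ANCOVA, with post-training BP or change as the response, adjusted for control-session ABPM or for control status by the article's ABPM limits. Alternatively, keep the repeated-measures model and add a control-status-by-time term. A control-status main effect alone would not do, because it leaves the group-by-time contrast unchanged. Either form assumes a similar gap in every arm; the plan should say so.

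For patients not yet allocated (the article reports recruitment as continuing), also keep two sets of sealed envelopes, by ABPM control status at the control session, in concealed permuted blocks of four. This holds the difference between arms to about 1 of 12 controlled patients, or 1/12 × 3 to 6 = 0.25-0.5 mmHg. For patients already allocated, the model term alone serves.

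Leave eligibility unchanged. No extra patients, visits or measurements are needed. The cost is one degree of freedom, a second envelope set, and arm sizes that may differ by up to two if the last block in each stratum does not fill. Blocks of eight would allow a difference of up to four, which is too much with 12 per arm.
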